### Randomisation

Due to the small number of clusters, participating GPs will be allocated to the intervention or control group using minimisation (incorporating a random element). Practices will be minimised based on practice size (small/large) and involvement with structured diabetes care (see Fig. 1). Baseline data collection of the cluster units (practices) will take place before allocation. Sequence generation and practice allocation will be carried out remotely by a statistician independent of the trial management team.

**Fig. 1 Fig1:**
[figure not shown]
Flow of practices through the DECIDE randomised pilot study

### Intervention

DECIDE is a complex intervention, which used the Medical Research Council framework for development of a complex intervention, using a theoretical base and incorporating the results of simulation and a practice pilot [36]. The intervention development phase was built upon the results of the systematic review, which showed that there was only one professionally targeted intervention for patients with poor control of T2DM and none using a CDSS [26]. All practices (control and intervention) will use the finder tool to identify the included patients in the study. Table 4 outlines the intervention components in the pilot cRCT. All medication changes, which are reflected in existing guidelines, will be at the discretion of the intervention GPs.

**Table 4 Tab4:** Components of the DECIDE intervention

a) A web-based decision CDSS was created which delivers patient-specific recommendations to the GP on what medication intensifications could be recommended, if appropriate. The algorithms in the CDSS are based on NICE guidance for management of hypertension and T2DM. The changes to the DECIDE intervention based upon the practice pilot study are outlined in Fig. 1. b) A training module was developed for intervention group GPs to explain all the steps in the intervention. Web-based training information and videos will be available on the DECIDE website, which houses the CDSS. An educational folder will be delivered to each GP on how to operate the CDSS.	

### Control

Control practices will continue to provide diabetes care as usual in their General Practice. They will have telephone contact from the research team to support baseline data collection. Their next contact will be at follow-up data collection, which will be at the same time as for intervention practices. Both control and intervention practices will receive a research stipend, to reflect the workload involved in the trial.

### Outcome measures

As this is a pilot study, we will ensure the feasibility and acceptability of the intervention with the GPs. The primary outcomes will be measures of feasibility such as recruitment and retention of practices and acceptability of the intervention to the GPs and also HbA1c, a measure of glycaemic control in the patient. Secondary outcomes will include changes in glycaemic medications, blood pressure medications, lipid-lowering medications and healthcare utilisation.

### Data collection

GPs and practice nurses will collect baseline data prior to allocation. Intervention GPs will then initiate the DECIDE pathway, over a 1-month window, as part of the T2DM Cycle of Care [36]. Anonymised demographics and patient information, such as patient gender and morbidity will be collected in the DECIDE website, by the practice nurse. No identifiable patient information will be made available to the researchers and will be collected for each patient at an individual level. Outcomes will be measured at 3-month follow-up, following the end of the initial 1-month intervention window.

### Sample size

As this is a pilot cRCT, a formal sample size calculation is not officially required [37]. However, based on the non-randomised feasibility study, we have calculated a provisional sample size required to estimate a clinically significant change in HBa1c. Participants in the non-randomised feasibility study who had poorly controlled T2DM had a mean baseline HbA1c of 91.1 mmol/mol (SD 16.7). Considering a clinically meaningful reduction of 10 mmol/mol in HbA1c, an intra-cluster coefficient (ICC) of 0.027 (based on a previous study [38]), using a power of 80% and allowing for a potential 10% loss to follow-up, we would need 14 practices with 10 patients in each practice giving a total of 140 patients.

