### Development of the DECIDE study and non-randomised feasibility study

We developed a theory-based complex intervention, called DECIDE: ComputeriseD dECisIonal support for poorly controlleD typE 2 Diabetes mellitus in Irish General Practice. The first stage of the UK Medical Research Council (MRC) framework was used to develop the intervention, using the Behaviour Change Wheel (BCW) as a theoretical guide to intervention development [33–35]. The intervention development is reported elsewhere and incorporates a CDSS element, which is professionally targeted at general practitioner (GP) prescribing behaviour, in the treatment of patients with poorly controlled T2DM [36].

We conducted a small-scale, uncontrolled, non-randomised feasibility study to assess the feasibility and acceptability of the DECIDE intervention within Irish General Practice [36]. Table 1 summarises the provision of T2DM healthcare in Ireland. Four GPs, including three academic GPs and one full-time clinical GP, piloted the DECIDE intervention. Each GP applied the intervention process to 15 different patients with poor control of T2DM. All practices were affiliated with the Health Research Board (HRB) Centre for Primary Care Research (http://www.hrbcentreprimarycare.ie). We included all patients who had both HbA1c > 70 mmol/mol and systolic blood pressure (SBP) > 150 mmHg or diastolic blood pressure (DBP) > 95 mmHg. Whilst there is no validated definition of poor control in the literature, we defined it as a HbA1c reading of ≥ 70 mmol/mol and a BP level of ≥ 150/95 mmHg [36]. When this number of patients was < 15, we included a stratified randomised sample of patients with only HbA1c > 70 mmol/mol or SBP > 150 mmHg or DBP > 95 mmHg. The list of 15 patients was kept anonymously within the practice.

**Table 1 Tab1:** Access to healthcare and structure of T2DM care in the Republic of Ireland

Access to general practice healthcare in the Republic of Ireland	

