The non-randomised feasibility study included 15 patients with poor control of T2DM per practice; the sample was generated through a random stratified number of the eligible patients with poor control of either glycaemic and/or BP risk factors. This was performed remotely with no identifiable patient information leaving the practice. The pilot GPs contacted the study team (MM and FB) with the number of persons included in the finder tool report and were informed which 15 patient IDs to include in the pilot study. The finder tool software was developed through a collaboration with the electronic health record (EHR)-vendors and the study team. Each practice was issued with a secure, specific login for the DECIDE website, which housed the CDSS. Approximately one clinical session was spent by pilot GPs performing the DECIDE intervention for all the included 15 patients. Firstly, GPs inserted clinical information for each patient into the DECIDE website, including anonymous baseline information and clinical information necessary for the CDSS (e.g. HbA1c, BP and medications). The second step for each patient involved analysing the suggested treatment intensification options from the CDSS on the DECIDE website. The options were based upon the Irish College of General Practitioners (ICGP) and National Institute for Health and Clinical Excellence (NICE) guidelines, linking the patient’s clinical information and medications to the evidence base for anti-glycaemic, anti-hypertensive and lipid-lowering medications [36]. Choosing an intensification option or acting on a recommendation was at the discretion of each GP.

A total of 37 patients from four practices with ‘poorly controlled’ T2DM received the DECIDE intervention and had complete data for analysis in the practice pilot study. Table 2 summarises the baseline patient’s demographics, highlighting the opportunities to intensify medications. The mean HbA1c was 83.9 mmol/mol, but most patients had mild hypertension (mean 141/83 mmHg) and a normal total cholesterol (mean 4.7 mmol/L). A substantial number of patients were either on no medications or monotherapy for glycaemic and BP management.

**Table 2 Tab2:** Summary of baseline characteristics and medications in the non-randomised feasibility study

Age	56.7 years (13.7) Mean (SD)		
Gender	Male (67%)		
Duration diabetes	7.1 years (5.3) Mean (SD)		
GMS Status	69.2%		
HbA1c level	83.9 mmol/mol (30.8) Mean (SD)		
SBP	140.9 mmHg (22.71) Mean (SD)		

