Feedback from GPs, through interviews and structured written feedback, reported successful patient identification facilitated by the finder tool. One pilot GP stated the ‘finder tool was excellent and the decisional support was educational’. Feedback indicated that the divisions of intensification options in terms of glycaemic, blood pressure and lipid-lowering medications were clear and useful. All GPs thought that the initial step, of inserting information from the EHR, could be enabled by the practice nurse, allowing the GP to review this information and to assess the treatment intensification options from the CDSS in the second step. For some patients, it was noted the biggest issue was not a pharmacological, clinical or intensification issue; the GPs reported that the reasons for poor control related to ‘logistics’ and ‘an educational and compliance deficit which is not easily fixed with a structured six-month review’. Using DECIDE was also felt to be very quick, which was positive.

We used the results of the non-randomised feasibility study to modify processes in the next phase of the DECIDE intervention (the pilot cluster RCT (cRCT)). Therapeutic intensification actions were deemed not possible in approximately one third of patients, due to complex social reasons. Other strategies or actions were suggested, including referral to a community-based diabetes nurse specialist, asking for more frequent reviews and contacts with the patient and addressing addiction or frailty issues. These non-pharmacological ‘actions’ were deemed important to explore and document, prior to considering therapeutic intensification options. The non-randomised feasibility study raised the issue of whether the study should include patients with elevated BP, but with controlled HBA1c, as was done in the non-randomised feasibility study. Based on the pilot results, we decided to target only patients with HbA1c > 70 mmol/mol, as only a small number of patients had both raised BP and HbA1c and including patients with very elevated BP would increase our sample size requirement significantly for the pilot cRCT. We also identified additional data to be collected at follow-up, including consultation visitation rate and frequency of review at hospital and with community diabetes nurse specialists. Table 3 outlines the major changes made to the intervention based upon the results of the non-randomised feasibility study.

**Table 3 Tab3:** Summary of DECIDE intervention changes

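### The SD of 16.7 behind the sample size is not reconciled with the SD of 30.8 reported for the same feasibility study, and it cannot come from that sample's HbA1c > 70 subset

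*Protocol article*

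**What the plan says.** The Sample size section of the protocol article plans on a "mean baseline HbA1c of 91.1" mmol/mol. The full statement is: "Participants in the non-randomised feasibility study who had poorly controlled T2DM had a mean baseline HbA1c of 91.1 mmol/mol (SD 16.7"). With a 10 mmol/mol difference, an ICC of 0.027, 80% power and 10% loss, it concludes that "we would need 14 practices with 10 patients in each practice giving a total of 140 patients".

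The section on development and the non-randomised feasibility study describes 37 patients, also labelled poorly controlled, who "received the DECIDE intervention and had complete data for analysis in the practice pilot study". For them it says: "The mean HbA1c was 83.9" mmol/mol. Table 2 gives "83.9 mmol/mol (30.8) Mean (SD").

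The same section offers two possible meanings of the label. It defines poor control by both criteria: "we defined it as a HbA1c reading of ≥ 70 mmol/mol and a BP level of ≥ 150/95 mmHg". It also says that the feasibility sample took in "patients with elevated BP, but with controlled HBA1c, as was done in the non-randomised feasibility study".

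No number of patients and no subgroup definition accompany the 91.1/16.7 pair.

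**The concern.** One study yields two HbA1c summaries under one label, and their variances differ by a factor of (30.8/16.7)² = 3.4. The required sample size is proportional to the variance, so the stated 80% power depends on which figure describes the patients the trial will enrol.

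A reader would assume that 91.1/16.7 is the HbA1c > 70 part of a mixed sample. If so, the choice of SD would be sensible and only the label would need tidying. The check below shows that this explanation does not work.

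HbA1c is named among the primary outcomes, and a potential effect on glycaemic control is one of the continuation criteria. The stated precision for HbA1c should therefore rest on a traceable input.

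**Working it through.** **1. Reproducing the plan's figure.** Inputs from the Sample size section: difference 10, SD 16.7, ICC 0.027, power 80%, loss 10%, 10 patients per practice. Assumed, because not stated there: two-sided alpha 0.05 and 7 practices per arm.

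- Per arm before clustering: 2 × 16.7² × (1.96 + 0.84)² / 10² ≈ 43.8, so 44.
- Design effect: 1 + 9 × 0.027 = 1.243.
- 44 × 1.243 / 0.9 = 60.8 per arm, or 6.08 practices, rounded up to 7. That gives 14 practices and 140 patients, so the plan's figure reproduces.

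**2. Power after loss, by SD.** With 9 evaluable patients per practice there are 63 per arm and the design effect is 1 + 8 × 0.027 = 1.216. SE = SD × √(2 × 1.216 / 63). The table is unadjusted for baseline; the half-width uses t with 12 df.

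| SD | SE | Power, normal | Power, t (12 df) | 95% CI half-width |
|---|---|---|---|---|
| 16.7 | 3.28 | 86% | 80% | 7.1 |
| 20 | 3.93 | 72% | 65% | 8.6 |
| 25 | 4.91 | 53% | 47% | 10.7 |
| 30.8 | 6.05 | 38% | 33% | 13.2 |

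**3. Can 91.1/16.7 be the HbA1c > 70 subset of the Table 2 sample?** Let n₁ of 37 patients have mean 91.1 and SD 16.7, and let the remaining n₂ = 37 − n₁ lie between 0 and 70.

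- Remainder mean: m₂ = (37 × 83.9 − 91.1 n₁) / n₂.
- Sum of squares that the remainder must supply: 36 × 30.8² − (n₁ − 1) × 16.7² − n₁ × (91.1 − 83.9)² − n₂ × (m₂ − 83.9)².
- Largest sum of squares possible for values in 0–70 with mean m₂: n₂ × (70 − m₂) × m₂.

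Results:

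- n₁ = 24 or fewer: m₂ exceeds 70 (70.6 at n₁ = 24), so the remainder is not at or below 70.
- n₁ = 25 to 34: the required sum of squares (23,462 falling to 3,209) always exceeds the possible maximum (467 to 6,529). At n₁ = 30, m₂ = 53.0 and the requirement is 34,151 − 8,088 − 1,555 − 6,666 ≈ 17,843, against a maximum of 6,296.
- n₁ = 35 or more: m₂ is negative.

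No split works. The largest whole-sample SD attainable is 29.5, even with a floor of 0, and 24.8 with a floor of 30. Repeating the check with 38 or 39 patients also finds no feasible split.

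**4. What remains possible.**

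- *A both-criteria subgroup.* Without the ceiling of 70 on the rest, the arithmetic can work. With 8 patients at 91.1/16.7 (an illustrative number), the other 29 would have mean 81.9 and SD 33.6.
- *An error in Table 2.* If 34 patients have 91.1/16.7 and 3 missing values are counted as zero, the 37 have mean 83.7 and SD 29.9. This is close to 83.9/30.8, though not exact. Table 2 has other loose figures: a GMS share of 69.2% cannot arise from 37 patients (25/37 = 67.6%, 26/37 = 70.3%), and the quadruple glycaemic therapy row shows n = 1 beside a breakdown of n = 3.

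**5. Effect of baseline adjustment.** The Data analysis section adjusts for baseline HbA1c. Multiplying the SE by √(1 − r²) at SD 30.8 gives normal-approximation power of about 48%, 64% and 79% for r = 0.5, 0.7 and 0.8. These correlations are assumptions; the article states none.

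**The case against.** The strongest reply is that the two figures need not conflict. The feasibility section's own definition requires both raised HbA1c and raised BP, and a subgroup defined that way is arithmetically possible. The Population section recruits such patients first, so they are not foreign to the trial. The denominator is also uncertain: Table 2 states 37 only for its medication rows, and the GMS share fits 27/39. The stated calculation is correct on its own inputs, is called provisional, and is described as not required for a pilot.

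Much of this stands. It rules out saying that the figures are irreconcilable. It does not remove the gap, because the article never says which group gave 16.7 or how many patients it held. A denominator of 38 or 39 does not rescue the HbA1c > 70 reading. If the both-criteria group is the source, the article itself says that only a small number of patients met both criteria. That group is also narrower than the population in the abstract and the Population section, which admit patients with only one raised measure.

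A reader might go further and infer that the design really has 33–38% power. The documents do not support that. The feasibility sample included patients with controlled HbA1c, so 30.8 is not shown to be the SD of the trial population. It may itself be a tabulation error, in which case 16.7 could be sound. The figure also ignores the planned baseline adjustment.

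**Conclusion.** The concern holds as an unexplained and possibly wrong planning input, not as an arithmetic error in the sample size. Either Table 2 is wrong, or the SD behind the stated 80% power comes from a group other than the HbA1c > 70 patients in that sample, such as those with both criteria raised.

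At SD 16.7 the design meets its target with little to spare on the t basis. Moderate increases in SD erode unadjusted power quickly, and SD 30.8 marks only a conditional worst case. These results assume two-sided 5%, 7 practices per arm, equal cluster sizes and 10% loss spread evenly.

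Severity is moderate: the calculation is labelled provisional, and continuation is based mainly on feasibility.

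**What to change.** - Reconcile the statement in the feasibility section that only patients with HbA1c > 70 mmol/mol are targeted with the Population section, which still admits patients with raised BP alone as a last tier. The relevant SD depends on this rule.
- Re-derive the HbA1c mean and SD from the feasibility records of patients who meet the settled rule, excluding missing values. State their number and definition.
- Correct whichever of Table 2 and the Sample size section is wrong, or explain in one sentence why the two differ.
- Restate power or, better for a pilot, the expected 95% CI half-width over a range of SDs: about 7 mmol/mol at 16.7 and 13 at 30.8, before baseline adjustment. State any baseline correlation that is assumed.

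The trial need not be enlarged. The cost is re-tabulating about 37 records and rewording one paragraph; the stated power may become less favourable.

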### Trial process

The intervention will take place over 1 month following allocation. Follow-up data collection will take place 4 months after the intervention finishes in the intervention practices and contemporaneously in control practices, by participating practice staff, including practice nurses.

### Blinding

Care providers cannot be blinded due to the nature of the intervention but contamination of patients will be prevented using a cluster design. Patients will be aware that their practice is participating in the study but as no individually identifiable patient data is being used, individual patient consent is not being sought. Blinding of outcome assessors will not be required for the primary outcome as it is collected using an automated objective laboratory measure (HbA1c).

### Data analysis

Practice and patient-chart information will be collected. Baseline data from the practice (cluster units) will be collected prior to allocation using a practice-based questionnaire. Patient-level outcomes will be collected after allocation, using the DECIDE website, inputted by the practice nurse, then general practitioner and anonymised at practice level. Due to the nature of the project and targeting of the intervention at cluster level, patient-reported outcome measures will not be collected, as this would be beyond the scope of the proposed project and would require individual patient consent.

All results will be collected at practice level by uploading anonymised patient data through the web-based DECIDE system. Patient data is recorded at the individual level. Initially, appropriate descriptive statistics (for example, means (SD), medians (IQR) and frequencies and percentages) will be used to assess balance between the intervention and control for both practice and patient characteristics. Descriptive statistics will also be used to assess measures of feasibility such as recruitment and retention of practices.

Mixed effects regression models will be used to account for the hierarchical nature of the data. The primary analysis is to estimate HbA1c for the intervention group versus the control, adjusting for baseline HbA1c and minimisation factors. A random effects linear regression will be used, including a random practice effect to account for the correlation between patients in practices. In a secondary analysis, we will further adjust for any variables displaying an imbalance between groups at baseline. Both intention to treat (i.e. including all randomised practices and patients, regardless of participation in the intervention) and per protocol analysis (to explore whether adherence to the intervention influences the effect of the intervention) will be conducted.

The above analyses will be repeated for secondary outcomes (BP, lipids), healthcare utilisation (including practice and hospital visitation rates) and medication intensification. All analyses will use appropriate (that is, logistic or linear) regression models, with results presented as point estimates (odds ratios or difference in means), 95% confidence intervals and *p* values. The primary analyses will involve intention-to-treat comparisons between the two groups, and a secondary per protocol analysis will also be conducted [39].

Furthermore, we will conduct subgroup analyses investigating whether there is any differential effect of the intervention based on gender and age (< 65 and ≥ 65). Data analysis will be conducted once all follow-up is complete. There are no planned interim analyses. Stata v14 will be used for all analyses [40].

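### With only 14 practices the article states no few-cluster inference method, and its rules on imbalance adjustment and on models for visit rates should be changed

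*Protocol article*

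**What the plan says.** Under Data analysis, HbA1c is compared between arms with adjustment for baseline HbA1c and the minimisation factors: "A random effects linear regression will be used, including a random practice effect to account for the correlation between patients in practices". The analyses are then repeated for blood pressure, lipids, healthcare utilisation (including practice and hospital visit rates) and medication intensification. On the type of model the text is: "All analyses will use appropriate (that is, logistic or linear) regression models". Results are to be given as odds ratios or differences in means, with 95% confidence intervals and p values. For the secondary model the rule is that "we will further adjust for any variables displaying an imbalance between groups at baseline"; balance is assessed on practice as well as patient characteristics.

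The size of the trial is given under Sample size: "we would need 14 practices with 10 patients in each practice giving a total of 140 patients". Under Randomisation, minimisation is chosen "Due to the small number of clusters". The software is Stata v14. The article does not state ML or REML, a normal or t reference, or a degrees-of-freedom method.

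**The concern.** The treatment effect is a contrast between practices, so its precision depends on how well the between-practice variance is estimated from 14 units. Maximum likelihood tends to underestimate that variance in small samples, and a normal reference ignores the uncertainty in it. Both push intervals to be too narrow. The article acknowledges the small number of practices when it chooses the allocation method, but says nothing about it when it commits to p values and intervals.

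Two rules in the same section add to this.

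- **Imbalance-driven adjustment.** The covariates are chosen after looking at the data. Imbalance does not show that a variable is prognostic, and with about 7 practices per arm chance imbalance in practice characteristics is to be expected. Each practice-level variable that enters costs a between-practice degree of freedom.
- **Visit rates.** These are counts. A linear model can estimate a difference in means but assumes constant variance, which skewed counts seldom meet. A logistic model discards the count. The listed effect measures leave no place for a rate ratio.

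At stake is the calibration of the intervals and p values for HbA1c (named among the primary outcomes) and the secondary outcomes. Some of these inform the continuation criteria.

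**Working it through.** **Inputs.** From Sample size: 14 practices of 10 patients, ICC 0.027, SD 16.7 mmol/mol, difference 10 mmol/mol, power 80%, loss 10%. Assumed because not stated: two-sided 5% level (in line with the 95% intervals), 1:1 allocation (7 v 7), two levels for each minimisation factor.

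**1. The plan's own figure.**
- Individually randomised: n per arm = 2 × (1.96 + 0.842)² × 16.7² / 10² = 43.8.
- Design effect 1 + (m − 1) × 0.027: 1.243 at m = 10, 1.216 at m = 9.
- Per arm with m = 10: 43.8 × 1.243 / 0.90 = 60.5, about 6 practices. The plain normal formula therefore gives about 12 practices, not 14.
- One extra practice per arm gives 7 per arm: 14 practices, 140 patients.
- Alternatively, with 7 practices per arm and 9 analysed in each, SE = 16.7 × √(2 × 1.216 / 63) = 3.28 and 10 / 3.28 = 3.05. Power is 79.9% with t on 12 df and 86.2% with a normal reference.

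So 140 is reproduced when a small-sample allowance is made.

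**2. Degrees of freedom.** 14 practices less intercept, arm and two practice-level factors: 14 − 4 = 10. The two-sided 5% critical value is 2.23 at 10 df. If practice-level variables are added because they look imbalanced, it becomes 2.31 at 8 df (two added) and 2.45 at 6 df (four added). The last step alone is 2.45 / 2.23 = 1.10, or 10% wider.

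**3. False-positive rate by simulation, linear model.** No treatment effect, 14 practices with 9 patients each (unequal sizes and m = 10 also tried), baseline-outcome association 0.5, two practice-level covariates, 4,000 to 10,000 trials in most settings. Nominal rate 5%.

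| ICC | ML, normal | REML, normal | REML, t on 10 df |
|---|---|---|---|
| 0 | 5.8% | 4.4% | 2.5% |
| 0.027 (protocol) | 7.2-7.9% | 5.2% to about 6% | 3.0-3.2% |
| 0.05 | 8.6-9.5% | 5.8-6.7% | 3.4-3.6% |
| 0.10 | 10.1-10.5% | 6.5-6.8% | 4.2% |

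The ranges cover separate runs. Monte Carlo error is about √(0.075 × 0.925 / 10,000) = 0.26 points at 10,000 trials. At ICC 0.027 maximum likelihood put the practice variance at zero in about two thirds of trials, and those trials are then analysed as if there were no clustering.

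**4. Logistic mixed model with a normal reference** (assumed event rate 40%, 700 trials per setting, Monte Carlo error about 0.8-1.1 points): 4.9% at ICC 0.027, 8.4% at 0.05, 8.7% at 0.10.

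**5. Visit rates and imbalance adjustment.** The article gives no visit distribution and does not say how many variables might be added, so no false-positive rate is attached to these two rules. They are judged on their wording.

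**The case against.** The strongest answer is that the article is silent, not wrong. A random practice effect is a standard and correct model for these data. The estimator and the degrees-of-freedom method are commonly left to an analysis plan, which is not shown. That stands: the few-cluster point can be put only conditionally.

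A reader might infer more, in three ways that the documents do not support.

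- **That the plan's tests run at 7-10%.** This requires maximum likelihood with a normal reference, which the article does not choose. The 10% end also requires an ICC of 0.10, about four times the stated value and nowhere in the document. REML with a normal reference is close to nominal at 0.027, and the logistic model shows no excess there.
- **That intervals ought to be 14% wider.** That is 2.228 / 1.96 = 1.14 and presumes a fixed t on 10 df. At ICC 0.027 that reference rejects only about 3%, so it over-corrects.
- **That 14 practices reach 80% power only under a t reference.** A normal reference gives 86.2%, which also meets 80%. If anything, the sample size suggests that few clusters were allowed for in planning.

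It is also fair that feasibility is the primary aim, that the imbalance adjustment belongs to a secondary analysis while the primary covariates are fixed in advance, and that visit rates are a secondary outcome. This lowers the severity. It does not answer the two written rules, because a later analysis plan could correct them only by departing from the article.

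**Conclusion.** The point holds in a limited form. The article commits to p values and 95% intervals from random-practice-effect models on 14 practices, with about 10 between-practice degrees of freedom, and states no few-cluster method. If the linear models were fitted by maximum likelihood with a normal reference, the false-positive rate would be about 7-8% at the protocol's ICC, and higher only if the ICC is larger. With REML and a normal reference it would be about 5-6%. These figures rest on a two-sided 5% level, 1:1 allocation, about 9 analysed patients per practice and a baseline association of 0.5.

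The imbalance-driven adjustment and the limit on models for visit rates are poor rules as written, whatever the unseen analysis plan says; their effect is not quantified.

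Severity is low. The effect on glycaemic control and medication intensification is one of five continuation considerations, framed as a potential effect, with no p-value or interval threshold for a miscalibrated test to trip.

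**What to change.** State in the analysis section or the analysis plan:

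- **Continuous outcomes:** REML with Satterthwaite or Kenward-Roger degrees of freedom.
- **Binary outcomes:** a comparable few-cluster method, such as a practice-level summary analysis with a t reference or a mixed logistic model with between-practice degrees of freedom.
- **Secondary adjustment:** replace the imbalance rule with a short list of prognostic patient-level covariates, fixed before outcome data are seen.
- **Visit counts:** a negative binomial or Poisson model with a practice random effect, reporting rate ratios, with the same care over few clusters; add rate ratios to the listed effect measures.

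The cost is a few sentences, with no added patients, data or design change. The downside is somewhat wider intervals that may be slightly conservative when the ICC is low. A fixed t on 10 df was the correction simulated; Satterthwaite and Kenward-Roger were not, so their exact behaviour here would need its own check.
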